## **Module 2**

Question 1: Do you think you have had a uveitis worsening or disease recurrence (relapse) in the past month?

Yes, no or uncertain. If yes, specify which eye and duration.

Question 2: Have you ever experienced newly occurred eye redness in the past month?

Yes, no or uncertain. If yes, specify which eye and duration.

Question 3: Have you ever experienced newly occurred eye pain in the past month?

Yes, no or uncertain. If yes, specify which eye and duration.

Question 4: Have you ever experienced new blurred vision or decreased vision in the past month?

Yes, no or uncertain. If yes, specify which eye and duration.

Question 5: Have you ever experienced newly occurred light sensitivity in the past month?

Yes, no or uncertain. If yes, specify which eye and duration.

Question 6: Have you ever had newly occurred dark, floating spots in your field of vision (floaters, specks or moving clouds in your vision) in the past month?

Yes, no or uncertain. If yes, specify which eye and duration.

Question 7: Have you ever experienced other ocular or systemic symptoms in the past month?

Yes, no or uncertain. If yes, specify where and duration.

Question 8: Have you been disease-free and discontinuing uveitis treatment for 3 months?

Yes or no. If yes, jump to Question 15.

Question 9: Have you already been received any dose of COVID-19 vaccination?

Yes or no. If no, participants will be recommended to keep away from getting vaccination at present and the conversation will be finished, otherwise continue on Question 10.

Question 10: Which COVID-19 vaccine did you get?

Sinovac (CoronaVac), Sinopharm, ZFSW Biologics Company, others (specifically), or uncertain.

Question 11: How many doses of COVID-19 vaccines have you already been received?

One, two, three or more (specific numbers).

Question 12: When did you get each dose of COVID-19 vaccines?

Participants will be asked to provide the specific date as far as possible.

Question 13: Have you finished all required doses of COVID-19 vaccines?

Yes or no. If the answer is no, continue on Question 14, otherwise finished.

Question 14: When do you plan to get the next vaccine?

Participants will be asked to provide their plan on specific date as far as possible. If participants answer they no longer intend to get the next vaccine, specific reasons should be provided. Questions finished.

Question 15: Have you already been received any dose of COVID-19 vaccination?

Yes or no. If yes, back to Question 10. If no, jump to Question 16.

Question 16: Why did not you get vaccinated?

Patients will be asked to provide the reason for not having COVID-19 vaccination. Not willing to get vaccination, willing to get vaccination but having not yet gone to the vaccination site (specific reasons for not going to the vaccination site required), having gone to the vaccination site but refused due to the lack of vaccines, having gone to the vaccination site but refused due to contraindication, other reasons (specifically). After completing this question, all participants will be encouraged to go to get vaccination as soon as possible on the phone, although they might have shown their unwillingness to get one.

At the end of phone call, if the patient answer yes to any of questions 1 to 7 in the Module 2, the patient will be instructed to come back to study site to complete in-person clinic visit for further evaluation and examination. Alternatively, the patient will also be allowed to go to local hospitals for evaluation and examination, but the patient need to send back the copies of all medical notes, records, laboratory or auxiliary examination reports from the local hospitals. **Participants will receive best medical judgment and proper treatment for worsening of the ocular or systemic conditions, including but not limited to step-up treatment, treatment interruptions even hospitalization. Nasopharyngeal swabs for RT-PCR testing of SARS-COV-2 will be performed on cases of hospitalization.** No matter where the evaluation is completed, patients will be instructed to undergo three mandatory ocular assessments, including **best-corrected visual acuity testing, slit-lamp biomicroscopy and ophthalmoscopy.** Mandatory materials send back from local hospitals include the medical record written by the attending doctor with signature and the prescription of that clinic visit. An adjudication committee who are unaware of group assignment will independently determine the endpoint according to these medical records from our study site or the local hospitals. **If clinically-confirmed uveitis worsening occurs, participants will be recommended to postpone subsequent vaccination until uveitis remission. If a patient assigned to the deferred vaccination group is vaccinated without remission of his/her ocular disease, we will no longer provide any recommendations on vaccination and implement assigned intervention strategies, this patient will only be observed later.**

The vaccination records of all participants, including doses, times and vaccine types, will be verified at the Month 3 visit by seeking data from the Health Code System which has a linkage to databases of routinely collected individual-level vaccination information held by the Local Health Administrative Committee.

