## **5.6 Follow-Up**

Routine follow-up encounters will then occur every month. Participants will complete trial visits primarily by telephone calls from the call center. However, all participants will need to complete an in-person clinic visit on the end of three months since baseline.

On phone call, patients will be asked to answer the following predetermined questions according to their randomization assignment. **Module 1** will be subjected to those in

prompt vaccination group, and **Module 2** will be subjected to those in deferred vaccination group.

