### **Module 1**

Question 1: Do you think you have had a uveitis worsening or disease recurrence (relapse) in the past month?

Yes, no or uncertain. If yes, specify which eye and duration.

Question 2: Have you ever experienced newly occurred eye redness in the past month?

Yes, no or uncertain. If yes, specify which eye and duration.

Question 3: Have you ever experienced newly occurred eye pain in the past month?

Yes, no or uncertain. If yes, specify which eye and duration.

Question 4: Have you ever experienced new blurred vision or decreased vision in the past month?

Yes, no or uncertain. If yes, specify which eye and duration.

Question 5: Have you ever experienced newly occurred light sensitivity in the past month?

Yes, no or uncertain. If yes, specify which eye and duration.

Question 6: Have you ever had newly occurred dark, floating spots in your field of vision (floaters, specks or moving clouds in your vision) in the past month?

Yes, no or uncertain. If yes, specify which eye and duration.

Question 7: Have you ever experienced other ocular or systemic symptoms in the past month?

Yes, no or uncertain. If yes, specify where and duration.

Question 8: Have you already been received any dose of COVID-19 vaccination?

Yes or no. If no, jump to Question 14.

Question 9: Which COVID-19 vaccine did you get?

Sinovac (CoronaVac), Sinopharm, ZFSW Biologics Company, others (specifically), or uncertain.

Question 10: How many doses of COVID-19 vaccines have you already been received?

One, two, three or more (specific numbers).

Question 11: When did you get each dose of COVID-19 vaccines?

Participants will be asked to provide the specific date as far as possible.

Question 12: Have you finished all required doses of COVID-19 vaccines?

Yes or no. If the answer is no, continue on Question 13, otherwise finished.

Question 13: When do you plan to get the next vaccine?

Participants will be asked to provide the specific date as far as possible. If participants answer they no longer intend to get the next vaccine, specific reasons should be provided. Questions finished.

Question 14: Why did not you get vaccinated?

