**Uveitis remission is defined as an inactive disease for 3 months after discontinuing all treatments for eye disease.**

- m. Vaccine inaccessibility, defined as proportion having gone to the vaccination site but refused due to the lack of vaccines, whereby this situation continues until the end of trial.
- n. Reasons for not yet vaccinated until the end of trial among those who should have been vaccinated per protocol.
- o. Change in anterior chamber cells from the Baseline to the end of three months.

- p. Change in vitreous haze from the Baseline to the end of three months.
- q. Change in best corrected visual acuity LogMAR score from the Baseline to the end of three months.

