- l. Proportion of uveitis remission throughout the trial.

Descriptive analysis will be used to report the proportion of uveitis remission between groups. Difference between proportions as well as its associated 95% CI will be estimated with the Wilson score method.

- m. Vaccine inaccessibility, defined as proportion having gone to the vaccination site but refused due to the lack of vaccines, whereby this situation continues until the end of trial.

Descriptive analysis will be used to report the proportion of vaccine

inaccessibility between groups. Difference between proportions as well as its associated 95% CI will be estimated with the Wilson score method.

- n. Reasons for not yet vaccinated until the end of trial among those who should have been vaccinated per protocol.

Descriptive analysis will be used to report the each reason for not yet vaccinated between groups. Difference between proportions as well as its associated 95% CI will be estimated with the Wilson score method.

- o. Change in anterior chamber cells from the Baseline to the end of three months.

Descriptive analysis will be used to report the proportion of two-grade increase in anterior chamber cells (a clinically meaningful change as described by the SUN working group) from the Baseline to the end of three months between groups. Difference between proportions as well as its associated 95% CI will be estimated with the Wilson score method.

- p. Change in vitreous haze from the Baseline to the end of three months.

Descriptive analysis will be used to report the proportion of two-grade increase in vitreous haze (a clinically meaningful change as described by the SUN working group) from the Baseline to the end of three months between groups. Difference between proportions as well as its associated 95% CI will be estimated with the Wilson score method.

- q. Change in best corrected visual acuity LogMAR score from the Baseline to the end of three months.

A generalized estimating equation (GEE) will be used analyze the least-squares mean changes by treatment group with accounting for the correlation between eyes of the same patient and baseline LogMAR score per eye. For non-numerical visual acuities, the following denotations will be used as previously described: finger count (FC) is assigned as 1.7 LogMAR, hand movement (HM) as 2.0

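### Vaccine inaccessibility (m) is compared between arms, but refusals in non-remitted, unvaccinated deferred-arm patients cannot be recorded; remission (l) has no stated source common to both arms

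*Supplement*

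**What the plan says.** Protocol 2.0, section 5.6, assigns Module 1 to the "prompt vaccination group, and Module 2 will be subjected to those in deferred vaccination group". Under the schedule in 5.10 the modules are used at Months 1, 2 and 3, at the end-of-trial call and at unscheduled visits.

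- **Module 1 (prompt).** There is no remission item. Its eighth item is "Question 8: Have you already been received any dose of COVID-19 vaccination", with the routing "Yes or no. If no, jump to Question 14". Question 14 asks why the patient is unvaccinated, and refusal at the site for lack of vaccine is one of its answer options.
- **Module 2 (deferred).** The eighth item is "Question 8: Have you been disease-free and discontinuing uveitis treatment for 3 months", with the routing "Yes or no. If yes, jump to Question 15". After a *no*, Question 9 asks about vaccination: "If no, participants will be recommended to keep away from getting vaccination at present and the conversation will be finished". The list of reasons appears only at Question 16, which is entered only from a *no* at Question 15, and Question 15 only from a *yes* at Question 8.

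Protocol 6.3 and SAP 3.2 define m without restricting it to patients who were due for vaccination. Outcome n (reasons for not being vaccinated) is restricted in that way. On outcome l the protocol states: "Uveitis remission is defined as an inactive disease for 3 months after discontinuing all treatments for eye disease". SAP 11.2 says of l: "Descriptive analysis will be used to report the proportion of uveitis remission between groups", and adds a difference with a Wilson-type 95% CI. It does the same for m.

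**The concern.** A between-arm difference is interpretable only if the event can be recorded in both arms. For m it cannot. A deferred patient who is not in remission, goes to a site anyway and is turned away leaves no trace in the study data. The counterpart in the prompt arm is counted. The reported difference then mixes two things: the strategy (fewer deferred patients go) and the questionnaire (some who go are never asked).

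For l the worry is weaker. The only item that asks about remission outright goes to one arm and rests on the patient's own account, whereas protocol 4.1 d defines inactive disease by examination grades. If that answer feeds l, the arms are measured differently. Remission is the event that releases deferred patients to vaccination, so readers will use l to judge whether deferral is workable.

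**Working it through.** The plan gives no figure for m or l, so there is nothing to reproduce. The check is the skip logic, followed by an illustration on assumed rates.

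**1. Can a refusal for lack of vaccine be recorded?**

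| Patient, unvaccinated | Prompt, Module 1 | Deferred, Module 2 |
|---|---|---|
| Reports remission | Not asked about remission; Q8 no → Q14: yes | Q8 yes → Q15 no → Q16: yes |
| Does not report remission | Q8 no → Q14: yes | Q8 no → Q9 no → call ends: **no** |

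Two possible back-ups do not close the gap. The Health Code check at Month 3 (end of 5.6) covers doses, times and vaccine types, not refusals. Module 2 Question 14 collects reasons for declining a further dose, but only from patients who already had one, and Module 1 Question 13 does the same.

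**2. Size for m.** Let q_P and q_D be the true proportions refused in the prompt and deferred arms, and r the share of refused deferred patients who answered *yes* to remission. All three are assumptions.

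- True difference = q_P − q_D
- Recorded difference = q_P − q_D × r
- Part due to routing = q_D × (1 − r)

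| q_D | r = 2% | r = 10% | r = 20% |
|---|---|---|---|
| 0% | 0 | 0 | 0 |
| 0.5% | 0.49 | 0.45 | 0.40 |
| 1% | 0.98 | 0.90 | 0.80 |
| 2% | 1.96 | 1.80 | 1.60 |
| 5% | 4.90 | 4.50 | 4.00 |

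(percentage points)

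If true refusal is set equal in both arms, with 657 per arm, whole-patient counts and the hybrid score interval, 5% refused and r = 10% gives 33 v 3 recorded: 4.6 points (95% CI 2.9 to 6.5). With 1% refused and r = 10% it is 7 v 1: 0.9 points (0.02 to 2.0). Equal refusal is the unfavourable end of the range, because the deferred arm is advised to wait.

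**3. Size for l.** Take true remission as 10% in both arms, fully captured in the deferred arm, and let c be the share captured in the prompt arm. Prompt minus deferred = 10% × (c − 1). Counts are out of 657.

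| c | Counts | Difference (95% CI), points |
|---|---|---|
| 0% | 0 v 66 | −10.0 (−12.6 to −7.9) |
| 50% | 33 v 66 | −5.0 (−7.9 to −2.2) |
| 80% | 53 v 66 | −2.0 (−5.1 to 1.1) |
| 100% | 66 v 66 | 0.0 (−3.3 to 3.3) |

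The result depends entirely on c, that is, on how far data held in both arms are used. The last row is what a common source gives when the true rates are equal.

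**The case against.** **For m.** A reader might infer that the whole gap is an artefact. The documents do not support that. Protocol 5.5 recommends that the deferred arm wait for remission, Module 2 repeats the advice, and m counts only refusals that persist to the end of the trial. Few deferred patients should attend a site, so a low count is largely what the strategy would produce. This limits the size but does not remove the defect: for those who do attend, the event cannot be recorded, and the data cannot show how many there were.

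**For l.** A reader might infer that the remission comparison is biased as planned. No passage makes Question 8 the source of l. Remission rests on examined inactivity. SAP 3.1 gives endpoint events to a committee unaware of assignment, working from medical records as well as call records. Both arms have the Month 3 examination and a treatment record at baseline and Month 3. Question 8 can be read as call routing only. This stands, and it makes the point on l conditional. What remains is that SAP 11.2 does not state the derivation, the treatment record is not scheduled at the Month 1 and 2 calls, and no stop date is specified.

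A reader might also suppose that deferred patients must answer *yes* to be vaccinated. They need not: the clinic only gives a recommendation, and a patient vaccinated before remission is simply observed.

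**On consequence.** SAP 11.1 plans no formal comparison of secondary outcomes and rules out inference from them. The symptom items (Questions 1 to 7) are the same in both modules, so the primary outcome is not touched. Both statements stand.

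**Conclusion.** The concern holds for m as a matter of structure: under the modules as written, refusals among unvaccinated, non-remitted deferred patients cannot be recorded, so the planned difference partly reflects routing whenever such refusals occur. Its size cannot be known from the documents. On the assumed ranges it runs from 0 to 4.9 points, and the low end is plausible given the advice to wait. The rest of any difference is the strategy itself.

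For l there is a risk of differential ascertainment, not a demonstrated bias. It disappears if one rule based on data from both arms is applied.

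Outcome n is not affected in the same way, since its restriction to patients due for vaccination matches the Module 2 routing. Both l and m are secondary and descriptive. This is a cheap improvement, not a threat to the trial's main result.

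**What to change.** - **Outcome m, preferred.** In both modules, before any arm-specific branch, ask every unvaccinated participant whether they went to a vaccination site and were turned away, and why.
- **Outcome m, alternative.** Drop the between-arm difference and report m only among those recommended to be vaccinated, as n already does. State the denominator in SAP 3.2 and 11.2.
- **Outcome l.** State in SAP 3.2 and 11.2 that remission is derived in both arms by one rule from the Month 3 examination and the treatment record, and add the treatment stop date as a recorded field. Keep Module 2 Question 8 for call routing only, not as outcome data.

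The cost is one added item on existing calls, one data field and a few lines of SAP text, with no new visit. Calls become slightly longer, and remission may be counted lower than by self-report.

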### 4.1 Inclusion Criteria

A subject will be eligible for study participation if she/he meets all of the following inclusion criteria:

- a. Aged 12 years or older
- b. Not yet vaccinated prior to the Screening.
- c. Diagnosed with any forms of uveitis in any eye.
- d. An **inactive disease** status (all the following criteria are met):
  - (1) **Anterior chamber cells of 0.5+ or less (See SUN criteria in Appendix I);**
  - (2) **Vitreous haze of 0.5+ or less (See NEI/SUN criteria in Appendix II);**
  - (3) **No active inflammatory choroidal or retinal vascular lesions.**

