## **5.5 Interventions**

Interventions will take place at the Baseline visit. The Primary Treating Ophthalmologist will provide the recommendation of COVID-19 vaccination to the subject according to randomization assignment. For those randomized to the prompt vaccination, subjects will be recommended to go to vaccination site and get COVID-19 vaccination as soon as possible. Our ophthalmologic clinic does not provide the vaccination service. We will only give the recommendation to patients. For those randomized to the deferred vaccination, subjects will be recommended to get COVID-19 vaccination after the remission of uveitis. **Remission is defined as an inactive disease for 3 months after discontinuing all treatments for eye disease.** At baseline, all patients will also be educated to immediately contact us by phone call once they experience any discomfort or have any new ocular symptoms of eye redness, eye pain, decreased vision, light sensitivity or fark, floating spots. We will ask questions as prespecified in **5.6 Follow-up** on the phone call.

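### In Module 2 a deferred-arm patient's own yes to Question 8 turns the advice from waiting to vaccinating, with no check against the 5.5 remission definition, even if the same call reports new eye symptoms

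*Supplement*

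**What the plan says.** Protocol 2.0, 5.5, sets the condition for vaccinating in the deferred arm: "Remission is defined as an inactive disease for 3 months after discontinuing all treatments for eye disease". Section 4.1 d describes inactive disease by examination findings: "Anterior chamber cells of 0.5+ or less", a similar limit on vitreous haze, and no active lesions.

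Follow-up is mostly remote (5.6): "Participants will complete trial visits primarily by telephone calls from the call center". The schedule in 5.10 marks no eye examination and no treatment record at Months 1 and 2. Both are marked at baseline and Month 3.

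Module 2 of 5.6 carries the deferred-arm advice. Questions 1 to 7 ask about worsening and new symptoms. The switch is "Question 8: Have you been disease-free and discontinuing uveitis treatment for 3 months", answered yes or no. After a no, an unvaccinated patient reaches Question 9, where "participants will be recommended to keep away from getting vaccination at present". After a yes, the script goes to Question 15 and, if the patient is unvaccinated, to Question 16, after which "all participants will be encouraged to go to get vaccination as soon as possible on the phone".

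The examination for symptomatic patients is arranged afterwards: "At the end of phone call, if the patient answer yes to any of questions 1 to 7 in the Module 2", the patient is asked to attend the study site or a local hospital. The script tells patients to postpone further doses only once worsening is clinically confirmed. The same questions are put to patients who phone between calls, since all are "educated to immediately contact us by phone call once they experience any discomfort or have any new ocular symptoms" (5.5).

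**The concern.** Deferral until remission is what defines the comparator. If staff can tell a deferred patient to vaccinate before remission on the strength of a misremembered stop date or a misjudged disease state, the trial itself delivers prompt-arm advice in the deferred arm. That differs from ordinary non-adherence, because it would come from following the script.

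There is also a participant-protection side. Protocol 1.2 names relapse as the main potential risk. Yet a deferred patient who reports new eye pain and then answers yes to Question 8 is urged to be vaccinated first and asked to come for examination second, and nothing tells the patient to wait for that examination.

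**Working it through.** **1. Routes through Module 2 for an unvaccinated patient**

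| Questions 1–7 | Question 8 | Advice on the call | What follows |
|---|---|---|---|
| all no | no | stay away | nothing further |
| any yes | no | stay away | examination arranged |
| all no | yes | vaccinate soon | nothing further |
| any yes | yes | vaccinate soon | examination arranged; postponement only if worsening is confirmed |

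The advice depends on Question 8 alone. No step in 5.5, 5.6 or 5.7 asks for a record, an examination or an ophthalmologist's view before the last two rows take effect.

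**2. Does the later examination act as a remission check?** It looks for worsening, which is a different standard. By grade, 6.3 a counts a change from 0 to 2+ or from 0.5+ to 3+. A patient who moves from 0.5+ to 2+ cells is no longer inactive under 4.1 d, but does not meet that grade criterion. Unless vision loss or a new lesion qualifies, the script contains no instruction to withdraw the encouragement. The treating doctor may still do so on clinical judgment.

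**3. What a simple look-up can establish.** Take 3 months as 90 days, calls at days 30 and 60, and the ±7-day window in 5.10.

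- Month 1 call: day 23 to 37. Remission requires treatment to have stopped at least 90 − 37 = 53 to 90 − 23 = 67 days before baseline.
- Month 2 call: day 53 to 67. The stop date must lie at least 90 − 67 = 23 to 90 − 53 = 37 days before baseline.
- The latest Month 2 call is day 67, which is under 90. Nobody on eye treatment at baseline can be in remission at either call, so a yes from such a patient is wrong and can be detected from the baseline record.

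**4. Size (illustration only).** The plan gives no figure on this point. The base is the planned hazard ratio of 1.5 with 80% power (9.1; SAP 5). By Schoenfeld's formula, events = 4(1.96 + 0.8416)² / (ln 1.5)² = 191.

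Assumptions:
- Deferred hazard λ₀ = −ln(0.90)/3 = 0.0351 per month.
- Prompt hazard 1.5 × λ₀ = 0.0527 per month.
- Dropout rate −ln(0.85)/3 = 0.0542 per month in both arms.
- A share x of the deferred arm is wrongly released at the Month 1 call and has the prompt hazard from month 1.5.

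The hazard ratio is the large-sample Cox value over 3 months, found numerically. Power = Φ(√191 × ln(HR)/2 − 1.96).

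| x | patients of 657 | HR | power | HR if half are vaccinated |
|---|---|---|---|---|
| 0 | 0 | 1.500 | 80.0% | 1.500 |
| 1% | 7 | 1.497 | 79.6% | 1.498 |
| 2% | 13 | 1.493 | 79.1% | 1.497 |
| 5% | 33 | 1.483 | 77.7% | 1.491 |
| 10% | 66 | 1.466 | 75.3% | 1.483 |

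If 10% deferred-arm events refers to three months, about 150 events are expected. Power then goes from 69.8% to 69.4%, 68.9%, 67.6% and 65.2%, so the loss is almost the same on either base.

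**The case against.** The strongest reply is that this is a pragmatic trial of recommendations. Deferred patients are told at baseline to vaccinate after remission, vaccination takes place elsewhere, and no clearance visit is part of the strategy. A patient who misjudges remission could act on the baseline advice without any call. That stands, and it is why ITT remains valid for the advice as delivered and why the added effect of Question 8 is smaller than the illustration assumes.

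The reply also limits the numbers. Patients in remission are excluded at entry, and a wrong release needs an unvaccinated patient to misstate three months of disease-free time off treatment. Many who do so with new symptoms would be contradicting themselves. A wrong answer at Month 3 cannot reach the primary outcome, because SAP 10 excludes later data. The larger shares in the table have no support in the documents.

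Module 1 has the same order of encouragement first and examination second, so the ordering is not peculiar to the deferred arm. But vaccinating before remission is the prompt arm's assigned strategy; in the deferred arm it departs from the assigned one.

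Two remedies would go too far. At Month 1 or 2 the latest study examination is usually the baseline one, at which every entrant had to be inactive, so checking a yes against it would add little. Holding the advice after any yes to Question 7 would catch non-ocular complaints. Neither is proposed here.

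What the reply does not answer is that the script has staff change the advice without consulting a record that could show the answer to be wrong.

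**Conclusion.** The point holds as a minor one. The written routing can lead staff to give prompt-arm advice to a deferred patient who is not in remission or who has just reported new eye symptoms, and no check against 5.5 is specified. This follows from the text alone.

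Its size is unknown and probably small. If 2% or fewer were wrongly released, the loss would be under 1 percentage point of power, given constant hazards, release at the Month 1 call and full uptake two weeks later.

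A reader might infer more, and the documents do not support it:

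- **Material power loss or a biased primary analysis.** No expected frequency is given, and ITT compares the advice actually delivered.
- **No safeguard at all.** Patients who know they are on treatment are told to stay away, a yes on symptoms leads to examination, and confirmed worsening brings advice to postpone.
- **A proven mismatch of definitions.** Question 8 speaks of uveitis treatment and 5.5 of all eye treatment. That is an ambiguity to align, not a shown discrepancy.

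**What to change.** 1. Word Question 8 to match the remission definition in 5.5.
2. In the baseline treatment record already scheduled in 5.10, note whether the patient is on any eye treatment and, if not, the date it stopped.
3. Before the Question 16 encouragement, check a yes against that record. Anyone on eye treatment at baseline cannot be in remission at the Month 1 or Month 2 call. Others need a stop date at least 3 months before the call. If the check fails, follow the branch for a no. Apply the same rule to symptom-triggered calls.
4. If any of Questions 1 to 6 is yes, or an ocular symptom is reported under Question 7, withhold the encouragement until the examination that 5.6 already requires has been done.

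The cost is one date field, a short look-up for each yes, and a wording change. No visit is added. Advice is briefly delayed for the few patients truly in remission who report new eye symptoms. The look-up settles treatment timing only. It cannot prove that a symptom-free patient's eye is inactive, and that limit is acceptable in a pragmatic trial.
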